### Methods: participants, interventions, and outcomes

#### Study setting

A total of 88 breast cancer patients undergoing radiation therapy will be recruited into the radiation oncology clinic and allocated to the experimental group (EG: Alantel) or the control group (CG: moisturizing cream), with an allocation ratio of 1:1 (see flowchart; Fig. 1). Both groups will receive a 15-session (3 weeks) hypofractionated radiation therapy, subject to the usual hygienic recommendations.

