#### Interventions

Once the patient has been included in the study and allocated to one of the two groups, the radiation oncologists will collect demographics and existing pathologies and perform an initial assessment of the skin to be irradiated before the start of radiation therapy. The radiation oncologist will administer the patient a Quality-of-Life Assessment Questionnaire (Skindex-29) [19] and inform the family physician of the patient’s details, identification code, and probable date of initiation of radiation therapy so that the family physician can contact the patient prior to the start of the treatment to schedule follow-up visits.

At each follow-up visit after sessions 5, 10, and 15 and 1 week after completion of radiation therapy, the family physician will perform the following actions:

Evaluate patients’ irradiated skin according to the common toxicity criteria of the cooperative skin group suggested by the RTOG Foundation (https://www.rtog.org) [18].Likewise, patients presenting with dermatitis will be asked to assess and quantify the discomfort and pain related to dermatitis symptoms and signs on an analog ordinal scale (from 1 to 10).Complete the Skindex-29 Quality of Life Questionnaire [19] (https://www.bibliopro.org/buscador/294/cuestionario-dermatologico-de-calidad-de-vida-skindex-29).Record adverse events (AE): Possible AE will be evaluated and reported during the study, and their causal relationship with the components of the cream will be assessed. If an adverse reaction is found, the researcher will evaluate the intensity and frequency of each episode and decide whether or not additional treatments are needed. These side effects will be notified to the Andalusian Pharmacovigilance Center through the yellow card alert system. If the physician considers it appropriate, the patient will be withdrawn from the study.

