**Secondary outcomes**	
Onset and duration of RD	Time of onset and duration of post-radiation dermatitis
Toxicity in patients’ irradiated skin	Common toxicity criteria of the cooperative group for skin suggested by the RTOG Foundation (https://www.rtog.org) [18]
Discomfort and pain concerning symptoms and signs related to dermatitis	Degree of skin discomfort caused by radiation. Subjective assessment and quantification by the patient on an ordinal scale (0 to 10) Pruritus, pain, itching, or peeling of the skin
Quality of life	Quality of life of patients with skin conditions Skindex-29 questionnaire [19]

In addition, secondary outcomes include the level of toxicity in patients’ irradiated skin. It will be assessed according to the common toxicity criteria of the cooperative group for skin suggested by the RTOG Foundation (https://www.rtog.org) [18] according to which toxicity is classified into five levels: 0 for no toxicity or no change; 1 for scattered macular or papular rash or erythema that is asymptomatic; 2 for scattered macular or papular rash or erythema with pruritus or other associated symptoms; 3 for symptomatic generalized macular, papular, or vesicular rash; and 4 for exfoliative dermatitis or ulcerative dermatitis.

The assessment of discomfort and pain concerning symptoms and signs related to dermatitis is based on the subjective assessment and quantification by the patient on an ordinal scale (range 0 to 10), the Visual Analogic Scale (VAS), answering the following question: What score would you rate from 0 (where 0 is the situation where you do not feel symptoms such as pruritus, pain, itching, or peeling of the skin) to 10 (where 10 is the situation where you notice the most symptoms) to your skin problem where do you have the lesion?

Quality of life will be assessed by completing the Skindex-29 questionnaire. Skindex-29 is a self-administered questionnaire to measure the quality of life of patients with skin conditions every 4 weeks, consisting of 29 items. The Spanish version of Skindex-29 has been validated [19].

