#### Sample size

Taking as reference those values provided in a previous study [20], the expected occurrence rate of RD (primary outcome variable) would be 46.7% in EG and 78.6% in CG, respectively; with a 1:1 allocation, accepting an alpha risk of 0.05 (5%) and a beta risk of 0.20 (20%), and assuming a follow-up loss rate of 20%, 88 eligible patients (44 in each group) are needed (calculations performed with the Granmo software version 7.12 in: https://www.imim.cat/ofertadeserveis/softwarepublic/granmo/, sample size for two independent proportions).

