## Statistical methods

After the mechanization and filtering of the data, a descriptive analysis will be performed that will include the characteristics of the studied population (sociodemographic variables) and outcome variables using measures of central tendency, dispersion, and position in the quantitative variables and tabulation and calculation of relative frequencies in qualitative variables. The calculation of the main estimators with their corresponding confidence intervals for 95% safety will also be performed. An intention-to-treat analysis will be performed. To minimize the problem of missing data, the analysis will be performed by dragging the data from the visit from which they are obtained to the following visits and to the final one. That is, the intent-to-treat analysis will include all participants assessed at least once after randomization. In addition, a per-protocol analysis will be performed, defined as the group of participants who comply with the procedure to be followed, including the use of the substances tested in the study, in at least 80%. A pre-post-intervention comparative analysis will then be performed with the endpoints used; for this, we will use means comparison tests taking into account the results obtained in each of the visits (parametric, such as ANOVA for repeated measures, if the variables follow a normal distribution—Shapiro-Wilk Test—or non-parametric, such as Friedman’s test, if they do not follow it), or proportion comparison test on qualitative variables, such as Pearson’s chi-square test or Fisher’s exact test (*p* < 0.05). Finally, the results will be statistically compared between groups using the log-rank test after estimating the survival curve with the Kaplan-Meier method. Multiple linear regression analysis-dependent variable: results obtained with the VAS, and the survival analysis, by Cox regression-dependent variables: RD or no; RD improvement vs. no improvement and cured vs. non-cured will be performed to evaluate the effect of the product, adjusting for the sociodemographic and clinical variables presumably predictive or confounding. Statistical analysis will be performed using SPSS v.17.0 and EPIDAT 4.1 packages.

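### The adjusted analysis of RD is a continuous-time Cox model on data seen at four visits, so its hazard ratio depends on a tie method that the protocol does not name

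*Protocol article*

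**What the plan says.** **Assessment.** In the Protocol article, Interventions, the family physician grades the irradiated skin "At each follow-up visit after sessions 5, 10, and 15 and 1 week after completion of radiation therapy". Table 1 marks presence or absence of RD at those four post-allocation time points only.

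**Onset.** Table 2 lists as a secondary outcome "Time of onset and duration of post-radiation dermatitis". Table 1 also has an item for RD evolution time, marked at the same four visits. Neither entry says whether onset may be dated between visits.

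**Analysis.** Statistical methods compares the groups by Kaplan-Meier and log-rank and also names chi-square or Fisher tests for proportions. For adjustment it names linear regression for the discomfort scale and, for RD, "the survival analysis, by Cox regression-dependent variables: RD or no; RD improvement vs. no improvement and cured vs. non-cured will be performed". No tie method and no grouped-time or interval-censored model is named.

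**Sample size.** This rests on a comparison of two proportions. The RD rate "would be 46.7% in EG and 78.6% in CG, respectively", and after a 20% allowance for loss "88 eligible patients (44 in each group) are needed".

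**The concern.** Standard Cox regression is built for event times that are essentially distinct. Here RD first seen at a visit began at some point since the previous one. If the visit date is used as the onset date, every event falls on one of four times. The partial likelihood then has to be approximated or redefined at each tied time, and the common choices give different answers when ties are this heavy.

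This Cox model is the only adjusted analysis named for the primary outcome, and the protocol gives it the task of evaluating the product's effect. At stake is whether that estimate and its test reflect the data or a software setting. Separately, an onset dated at the visit where RD is first seen is late under any tie method.

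**Working it through.** **1. Reproduce the stated sample size.** Inputs from Sample size: 0.467 and 0.786, alpha 0.05 (taken as two-sided, since sidedness is not stated), power 80%, 1:1 allocation, 20% loss. The pooled-variance formula without continuity correction is

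n = [1.960·√(2·p̄·q̄) + 0.842·√(p₁q₁ + p₂q₂)]² / (p₂ − p₁)²

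With p̄ = 0.6265 this is (1.341 + 0.544)² / 0.319² ≈ 34.9, so 35 per arm. Then 35/0.80 = 43.75, so 44 per arm and 88 in total. The stated figure is reproduced.

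**2. Expected events.** 35 × 0.467 = 16.3 and 35 × 0.786 = 27.5, about 44 events in 70 evaluable patients.

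**3. Implied hazard ratio.** The protocol states none. Under proportional hazards, HR = ln(1 − 0.467)/ln(1 − 0.786) = −0.629/−1.542 = 0.408.

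**4. Group onset to the visits.** Assumed cumulative hazard in control: 1.542·(t/22)^k, with Weibull shape k = 1, 2 or 3 and visits at days 5, 10, 15 and 22 as labelled in Table 1. Expected events at the four visits, both arms together:

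- k = 1: 15.0, 11.3, 8.6, 8.9
- k = 2: 3.8, 10.0, 13.0, 17.1
- k = 3: 0.9, 5.8, 13.1, 24.0

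**5. Fit the same grouped data in different ways.** 35 per arm, 3,000 simulated trials per shape. Cells show median HR and power for k = 1 / 2 / 3.

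| Analysis | HR | Power |
|---|---|---|
| Cox, ungrouped onset | 0.409 / 0.411 / 0.404 | 83% / 84% / 83% |
| Cox, Breslow ties | 0.455 / 0.471 / 0.489 | 75% / 72% / 67% |
| Cox, Efron ties | 0.411 / 0.416 / 0.413 | 82% / 83% / 82% |
| Cox, exact-discrete ties (an odds ratio) | 0.365 / 0.354 / 0.329 | 83% / 83% / 82% |
| Grouped-time complementary log-log | 0.404 / 0.408 / 0.397 | 83% / 84% / 83% |
| Log-rank, grouped | – | 83% / 84% / 83% |
| Two-proportion test | – | 80% / 81% / 81% |

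**6. Bias or small-sample noise?** The large-sample limits, solved numerically for k = 1, 2, 3, are 0.454, 0.470, 0.493 for Breslow (log HR shrunk by 12% to 21%) and 0.410, 0.413, 0.417 for Efron (shrunk by 0.5% to 2.4%). The Breslow shift is bias.

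**7. Under no effect** (k = 2), the rejection rate is 1.1% with Breslow, 4.8% with Efron, 5.6% with complementary log-log and 5.1% with log-rank.

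**8. Sensitivity.**
- If all 44 per arm are analysed (k = 2), power is 83.8% with Breslow, 90.5% with Efron and 91.0% with complementary log-log.
- A simulation with other timing assumptions (cumulative-hazard shares by visit of 25/25/25/25, 5/15/35/45 and 2/8/30/60; 600 trials each; geometric mean HR) gave Breslow 0.452–0.464 and 70–74%, Efron 0.395–0.408 and 82–83%, and complementary log-log 0.383–0.402 and 82–85%.
- A further repeat at 35 per arm gave Breslow 0.46–0.48 and 68–74%, Efron 0.41–0.42 and 81–84%, and complementary log-log 0.40–0.41 and 82–85%.

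**9. Lateness of onset.** If onset is uniform between visits, the mean delay is half the gap: 5/2 = 2.5 days to 7/2 = 3.5 days.

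**The case against.** Four arguments carry weight.

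- **Ties as such do no harm.** A reader might infer that so many ties must pull the hazard ratio toward 1 and cost power. That is not so: Efron ties leave both nearly intact, and the exact-discrete method moves the estimate away from 1. The harm is specific to Breslow. The protocol names no tie method, and the documents do not show that the named software would apply Breslow.
- **The planned power is intact.** A reader might infer that the trial falls short of its 80%. The sample size rests on two proportions, and both that test and the grouped log-rank test hold their power. No power was planned for the adjusted model.
- **Onset may be dated between visits.** Table 2 and the RD evolution time item leave this open, so four onset values are likely rather than certain. Against it, no diary is described, the item is collected at the same four visits, and grade 1 includes asymptomatic erythema. That such erythema is hard to date by recall is an inference.
- **Tie handling belongs in an analysis plan, and the shift is modest.** With 16.3 and 27.5 events, SE(log HR) ≈ √(1/16.3 + 1/27.5) = 0.31. The large-sample Breslow shift is ln(0.454/0.408) = 0.11 to ln(0.493/0.408) = 0.19, or about 0.3 to 0.6 SE, and toward no effect. Efron also does about as well as the grouped-time model, so abandoning Cox is not essential.

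All four limit the claim. They do not remove it, because the article itself fixes both the visit schedule and a continuous-time model that does not match it. An unnamed tie method alone would not be a finding.

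**Conclusion.** The point holds in a conditional form. Provided onset is dated by visit, about 44 events share four times and the adjusted hazard ratio for RD depends on the tie method. Across the runs it is about 0.45–0.49 with 67–75% power under Breslow, and about 0.40–0.42 with 81–84% power under Efron, against an implied 0.41. The exact-discrete method would report an odds ratio of about 0.33–0.37. The exposure is confined to the adjusted Cox analysis.

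These figures assume proportional hazards at the design rates, the event-timing patterns shown, and 35 analysed per arm. Cox uses only the order of event times. Whether visits are counted in sessions or calendar days (15 sessions over three weeks, but day 15 in Table 1) therefore affects only how events split across visits. Late dating of onset is common to both arms: it affects the reported time of onset but is not shown to bias the comparison. The issue is worth correcting because the correction is nearly free; it does not threaten the trial.

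**What to change.** - State how onset is dated: by the visit at which RD was first seen, or by a recorded date between visits.
- If by visit, analyse RD with a grouped-time proportional-hazards model: binomial regression with complementary log-log link, one record per patient per visit while still at risk, with visit as a factor, treatment and the planned covariates. It estimates the same hazard ratio from visit-level data.
- Alternatively, keep Cox regression, specify Efron ties, and run it in software that offers them.
- Report time of onset as the visit at which RD was first seen, or by an interval-censored estimate.

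The cost is a few words in Statistical methods and a few lines of code. No new data, visits or patients are needed, and the log-rank and proportion tests stay as they are.

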## Oversight and monitoring

### Composition of the coordinating center and trial steering committee

The Project Coordination Commission comprises the management team, which consists of 6 members who meet every 2 months to review the trial status. It is composed of the principal investigator of the project ([name], epidemiologist), [name] [name] (epidemiologist expert in methodology and statistics), [name] (oncologist from the radiotherapy oncology service), and three family doctors ([name], [name] [name], and [name]).

Important modifications made to the initial protocol will be communicated to the funding body and the Ethics Committee and will be registered in clinicaltrials.gov.

### Adverse event reporting and harms

Possible AE will be evaluated and reported during the study, and their causal relationship with the components of the cream will be assessed. If an AE is found, the researcher will evaluate the intensity and frequency of each episode and decide whether additional treatments are needed. These AE will be notified to the Andalusian Pharmacovigilance Center and the Ethics Committee of the Reina Sofia Hospital (Cordoba, Spain). If the physician considers it appropriate, the patient will be withdrawn from the study.

## Dissemination plans

Study results will be communicated to clinical stakeholders and disseminated in communications at scientific events and through publications in peer-reviewed scientific journals. The final results will also be disseminated to the health professionals involved in the care of this type of patient through the internal communication channels of the Andalusian Health Service.

## Discussion

By carrying out this clinical trial, it is expected to verify that Alantel cream, based on natural products at high concentrations, has advantages over a moisturizing cream for the preventive and curative treatment of RD in patients with breast cancer. One of the main limitations of this study will be the time required to recruit the patients from the planned sample because the selection criteria are restrictive, and although the study is multicenter, recruitment will be coordinated through a single service of radiotherapy oncology. The COVID-19 pandemic caused the study to be delayed and could not start at the scheduled time. In addition, this influenced the patient recruitment process because accessibility to the health system was restricted and the research staff suffered an increase in the demand for care, focusing their efforts on the care of cancer patients with COVID-19.

## Trial status

The study was intended to start in 2019, but was interrupted due to the COVID-19 pandemic. The pilot study was conducted between July and September 2021, the training sessions for field researchers were held in October 2021, and the study concluded in June 2023.

## Abbreviations

RD: Radiation-induced dermatitis
EG: Experimental group
CG: Control group
GP: General practitioner
PC: Primary care
AE: Adverse events
